### Qualitative evaluation

Another unique component of this study is that we integrated qualitative research with the randomized controlled trial design. At the completion of the trial we will conduct focus groups to assess participants’ overall impressions of the intervention. More specifically, we will conduct four focus groups (two with each arm) with a sample of eight to ten participants in each group 6 months after completion of the study to ascertain the following: what did participants like and not like about the intervention? How could it have been done better? Which components were most responsible for promoting changes? Why did some seek an assessment of sleep apnea (and used CPAP) while others did not? Which intervention components were most and least acceptable? Were there any critical incidents that prompted respondents to get a sleep apnea assessment? How could the intervention be changed to make it more effective? A semi-structured interview guide will be developed based on our formative research conducted prior to the start of the intervention.

### Measures

#### Sociodemographic variables

Sociodemographic variables will include age, type of health insurance, marital status, education, place of birth (for example, US versus Caribbean), years in current residence and locality, number of children living in household, number of adults living in household, self-described ethnicity, and annual household income.

#### Apnea-risk evaluation system questionnaire

This tool includes questions on sleep patterns, daytime functioning, knowledge of sleep apnea, and diseases associated with sleep apnea (that is, HTN, DM, heart disease) [23].

#### Epworth sleepiness scale

This questionnaire uses a Likert-type scale in which the respondent indicates the most appropriate number ranging from 0 = would never doze or sleep to 3 = high chance of dozing or sleeping based on a given situation. A score of 10 or more is considered excessive sleepiness [32].

#### Apnea knowledge test and apnea beliefs scale

These two questionnaires assess participants’ understanding and beliefs of obstructive sleep apnea and CPAP treatment. The AKT includes 13 questions with a yes/no response choice and 2 open-ended questions; the ABS includes 24 items on a five-point Likert scale ranging from 'strongly agree' to 'strongly disagree'. A higher score on the AKT indicates better knowledge and understanding of the illness and treatment and a higher score on the ABS indicates greater likelihood of adherence to treatment [33].

#### Change assessment scale

This is a 32-item instrument that assesses a person’s readiness to change. Participants evaluate the extent to which they strongly agree or strongly disagree with various statements such as, 'I’ve been thinking that I might want to change something about myself' and 'I have problems and I really think I should work on them' [34].

#### Medical history

Medical history includes family history of sleep disorders, obesity, DM, HTN, dyslipidemia, and CVD; history of other preventive behaviors (for example, prostate exams), and other health behaviors (for example, regularity of physical examinations, cholesterol screening, smoking and drinking habits, and exercise habits).

#### Adherence to CPAP

We will assess CPAP adherence using subjective and objective measures. A self-report scale will be used to track CPAP adherence at the end of the 6-month period. CPAP adherence is defined as the mean number of hours per day and days per week participants report using CPAP [35,36] (adherence: > 4 hours a night for 70% of the nights or no report of symptomatic complaints). Throughout the study, CPAP adherence data will be electronically monitored on a daily basis. Data will be downloaded directly from CPAP devices [37].

A complete list of measures and the data collection schedule is provided in Table 2.

**Table 2 T2:** Schedule to acquire study data

**Outcome measures**	**Baseline**	**First follow-up**^ **a** ^	**Second follow-up**
Sociodemographic and clinical variables	X		
Apnea-risk evaluation system questionnaire	X		
Epworth sleepiness scale		X	X
CES-D	X	X	
Apnea knowledge test	X	X	
Apnea beliefs scale	X	X	
Medical outcomes study short form 36	X		
Self-efficacy scale	X	X	
Change assessment scale	X		
Functional outcomes in sleep questionnaire	X	X	
Process variables	X	X	
*Post hoc* evaluation variables			X
Sleep variables (chart audit)		X	

^a^Follow-up outcome ascertainment is performed by the Data Manager at 6 months post-enrollment and at 6 months post-telephone intervention (TTI).

Cardio-metabolic measures are as follows. (1) Weight will be measured without shoes and using a validated digital scale. (2) Waist circumference will be measured by 1) locating the upper hip bone and the top of the right iliac crest, 2) placing the measuring tape horizontally around the abdomen at the level of the iliac crest (tape is snug without causing compression), and 3) measuring at the end of a normal expiration. (3) BP measurements will be taken following American Heart Association guidelines [38]. Using a BPTru automated BP monitor, five readings will be obtained while participants are seated comfortably for five minutes prior to measurement [39]; the average BP will be used as the BP index for each visit. (4) Following the National Cholesterol Education Program standard guidelines for total cholesterol measurement, we will use the Cholestech LDX Analyzer; whole blood from fingersticks will be used for the quantitative determination of HDL-C and FPG utilizing established formulation [40]. All measurements will be collected by trained clinical research staff.

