### Outcomes

The primary outcome will be adherence to physician-recommended assessment and treatment for sleep apnea. The secondary outcomes will include 1) maintenance of recommended treatment at 6 months and at 12 months; 2) waist circumference; 3) lipid levels; 4) BP; and 5) FPG or HbA1c for those who have a DM diagnosis. Outcomes assessment will be conducted at baseline, and at 6- and 12-months post-randomization.

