### Statistical analysis

To describe the characteristics of the study population, we will use measures of central tendencies and dispersion for continuous data; frequency distributions will be used for categorical data. Chi-square tests will be used to compare categorical data, and ANOVA will be used for continuous data. Relationships between mediators of adherence to recommended sleep apnea assessment and CPAP treatment will be examined using binary multivariate logistic regression analysis. The two main dependent measures will be: adherence to physician-recommended sleep assessment (yes versus no) and adherence to CPAP treatment (yes versus no). Candidate mediators will include sleep apnea knowledge, self-efficacy, readiness, and trust/rapport with the HE. Effects of sociodemographic and clinical factors will be adjusted in those analyses. Repeated-measures MANCOVA will be used to examine differences between baseline and follow-up measures (for example, waist circumference (WC), BP, HDL-C, FBG/HbA1c); age, sex, and sleepiness will be entered as covariates. MANCOVA is a robust technique that incorporates routines to account for heterogeneous variances, serial correlations, and variance inflation [41].

### Hypothesis 1

TTI will lead to higher rates of sleep apnea assessment at 6 months. A comprehensive assessment of sleep apnea will be defined by documentation of an appropriate medical and sleep history by a sleep clinician and a nocturnal polysomnographic study.

#### Analysis for hypothesis 1

Analysis will be performed on an intention-to-treat basis. All participants in the treatment arm will be assumed to have received the full dose of the telephone intervention and all participants in the attention-control arm will be assumed to have received no tailored intervention. Prior to testing for intervention effects, we will verify the comparability of the treatment and control arms with respect to all available demographic and personal data. T-tests and chi-square tests will be used for continuous and categorical variables, respectively. Thus, receipt of sleep apnea assessments within the 6-month period will be a binary outcome, yes or no. We will use logistic regression to estimate the odds associated with receipt of sleep apnea assessment contrasting the two study arms.

### Hypothesis 2

TTI will lead to higher adherence rates to recommended follow-up care (that is, CPAP use (> 4 hours a night for 70% of the nights)) post-diagnosis of sleep apnea.

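### CPAP adherence has two conflicting definitions, and the one in Measures counts a non-user without complaints as adherent

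*Protocol article*

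**What the plan says.** Under Measures, Adherence to CPAP, the protocol article describes the variable in three ways.

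- A self-reported quantity: "CPAP adherence is defined as the mean number of hours per day and days per week participants report using CPAP".
- A yes/no rule in parentheses in the same sentence: "adherence: > 4 hours a night for 70% of the nights or no report of symptomatic complaints".
- Two data sources: "A self-report scale will be used to track CPAP adherence at the end of the 6-month period", and "Throughout the study, CPAP adherence data will be electronically monitored on a daily basis", with downloads taken from the devices.

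Under Statistical analysis, Hypothesis 2 describes the outcome as "CPAP use (> 4 hours a night for 70% of the nights)) post-diagnosis of sleep apnea". The symptom alternative does not appear there. The same section lists "adherence to CPAP treatment (yes versus no") as one of two main dependent measures, and the analysis for Hypothesis 2 is a logistic regression.

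The Outcomes section states: "The primary outcome will be adherence to physician-recommended assessment and treatment for sleep apnea". Treatment adherence is therefore part of the stated primary outcome, although Power and sample size calculations names documented receipt of a sleep apnea assessment as the primary study outcome.

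**The concern.** The two parts of the Measures rule are joined by an unrestricted alternative. The second part needs no CPAP use at all. It is also unclear whether it means symptoms of sleep apnea or complaints about the device, but a non-user can be free of either. Under this rule the variable mixes use of the treatment with absence of complaints. Hypothesis 2 does not mix them, so one participant can have two different values of the same main outcome.

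Two things are at stake. First, how participants are coded depends on which section the analyst follows, and the article does not say. Second, if the Measures rule is followed, the comparison between arms is distorted.

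A related weakness is the data source. The Measures definition is worded in hours that participants report, while objective daily data are collected as well, and the article does not say which source decides the yes/no value. The tailored-telephone arm is coached on CPAP adherence (Phase II); the control calls give information without tailored behavior-change strategies (Description of the attention-control arm). Coaching could inflate self-reported use in the intervention arm.

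**Working it through.** **1. The two rules applied to one participant.** Take a diagnosed participant with 0 hours of CPAP use and no complaints.

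- Measures: (hours threshold met = false) OR (no complaints = true) gives adherent.
- Hypothesis 2: hours threshold met = false gives non-adherent.

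The result is the same for anyone below the threshold who reports no complaints, including occasional users. This step uses only the text and needs no assumed figure.

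**2. Effect on a difference between arms, if the Measures rule is applied.** The article gives no expected CPAP adherence rates, so there is no planned figure to reproduce. Let p be the proportion meeting the hours threshold in an arm, and s the share of the remainder who report no complaints.

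Observed rate = p + s(1 − p).

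With the same s in both arms, observed difference = (1 − s) × true difference.

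**3. Inputs for an illustration.**

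- Rates of 35% and 47%, a difference of 12 points. These are the assessment-endpoint rates in Power and sample size calculations, borrowed here as an assumption.
- s = 10% to 25%, an assumption. The only related figures are in Study sites/population, where a random subsample of 70 registry members reported snoring (72%), excessive daytime sleepiness (65%) and difficulty maintaining sleep (75%). Since 75% had the last of these, at most 100% − 75% = 25% of that subsample could be free of all three.

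**4. Equal s in both arms.**

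- s = 10%: control 0.35 + 0.10 × 0.65 = 41.5%; intervention 0.47 + 0.10 × 0.53 = 52.3%; difference 10.8 points.
- s = 25%: control 0.35 + 0.25 × 0.65 = 51.25%; intervention 0.47 + 0.25 × 0.53 = 60.25%; difference 9.0 points.

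Among control participants counted as adherent, the share who qualify by the symptom alternative alone is 0.065 / 0.415 = 15.7% at s = 10%, and 0.1625 / 0.5125 = 31.7% at s = 25%.

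**5. Unequal s.** The same four rates, combined the other way, show that the direction is not fixed.

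- s = 25% in control and 10% in intervention: 52.3% − 51.25% = 1.05 points.
- s = 10% in control and 25% in intervention: 60.25% − 41.5% = 18.75 points.

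A true 12-point difference could almost vanish or be exaggerated.

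**The case against.** The best defence is that Hypothesis 2 has its own definition, that this definition measures use, and that a hypothesis-specific definition should govern its own analysis. A reader might infer from the Measures rule that the Hypothesis 2 endpoint does not measure CPAP use. The documents do not support that: the Hypothesis 2 text contains the hours threshold and nothing else. The harm arises only if the Measures rule is applied. What remains is that Measures is where the variable is defined, and nothing ranks one section over the other.

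A second defence is that the symptom alternative was meant only for people already using the device. The text does not say so, and even then someone with minimal use and no complaints would count as adherent.

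On the data source, the article does commit to subjective and objective measures and to device downloads. Which source feeds the analysis is a detail that an article may leave to the full protocol or analysis plan. That objection largely stands for the source taken alone. It does not answer the conflict between two stated rules.

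Three further inferences would go too far.

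- A reader might take participants to be documented as unblinded. Randomization says only that the health educator is not blind, and controls also receive up to 10 calls. Greater over-reporting in the intervention arm is plausible but is not documented.
- A reader might take 35% as a symptom-free share, because 65% of the subsample reported daytime sleepiness. That rests on one symptom; on all three listed symptoms the ceiling in that subsample is 25%. The subsample was also drawn from the registry, with 59% at high risk, and does not consist of diagnosed participants who fell short on CPAP use.
- A reader might think that the sample size is undermined. It is based on receipt of a sleep assessment, which this definition does not touch.

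**Conclusion.** The concern holds as a conflict between two stated definitions of a main dependent measure, one of which classes a non-user without complaints as adherent. This conclusion follows from the wording and depends on no assumed number.

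The size of any distortion cannot be fixed from the documents. It arises only if the Measures rule is used. With an equal symptom-free share of 10% to 25% below the threshold in both arms, an assumed 12-point difference becomes 10.8 to 9.0 points, a loss of 10% to 25% of the effect. The 12 points are borrowed from another endpoint, and the share is an assumption guided by a screening subsample. With unequal shares the bias can go in either direction. Inflated self-report in the coached arm is a further risk if reported hours decide the outcome.

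**What to change.** Reconcile Measures (Adherence to CPAP) and Hypothesis 2 into one outcome definition:

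- Delete the symptom alternative from the Measures rule.
- Use the hours threshold that both sections already share: more than 4 hours a night for 70% of nights.
- State that the yes/no value is determined from the device downloads already collected.
- Keep self-reported use and symptoms as supportive outcomes, reported separately.

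No new data collection is needed. The costs are that adherence rates will look lower than under the Measures rule, and that redefining a main outcome late in the trial needs a documented amendment. Trial status reports 311 participants randomized out of a planned 340 or so, so the amendment should be dated and in place before outcomes are analysed.

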### Outcomes

The primary outcome will be adherence to physician-recommended assessment and treatment for sleep apnea. The secondary outcomes will include 1) maintenance of recommended treatment at 6 months and at 12 months; 2) waist circumference; 3) lipid levels; 4) BP; and 5) FPG or HbA1c for those who have a DM diagnosis. Outcomes assessment will be conducted at baseline, and at 6- and 12-months post-randomization.

### Chart audit

Upon completion of a sleep assessment, a participant’s chart (intervention or attention control) will be subjected to a random audit. Audits for confirming self-report will be conducted by one of the study investigators, who will be blinded to randomization status. Verification of a sleep assessment entails documentation of an appropriate sleep history and a polysomnographic study.

### Statistical analysis

To describe the characteristics of the study population, we will use measures of central tendencies and dispersion for continuous data; frequency distributions will be used for categorical data. Chi-square tests will be used to compare categorical data, and ANOVA will be used for continuous data. Relationships between mediators of adherence to recommended sleep apnea assessment and CPAP treatment will be examined using binary multivariate logistic regression analysis. The two main dependent measures will be: adherence to physician-recommended sleep assessment (yes versus no) and adherence to CPAP treatment (yes versus no). Candidate mediators will include sleep apnea knowledge, self-efficacy, readiness, and trust/rapport with the HE. Effects of sociodemographic and clinical factors will be adjusted in those analyses. Repeated-measures MANCOVA will be used to examine differences between baseline and follow-up measures (for example, waist circumference (WC), BP, HDL-C, FBG/HbA1c); age, sex, and sleepiness will be entered as covariates. MANCOVA is a robust technique that incorporates routines to account for heterogeneous variances, serial correlations, and variance inflation [41].

### Hypothesis 1

TTI will lead to higher rates of sleep apnea assessment at 6 months. A comprehensive assessment of sleep apnea will be defined by documentation of an appropriate medical and sleep history by a sleep clinician and a nocturnal polysomnographic study.

#### Analysis for hypothesis 1

Analysis will be performed on an intention-to-treat basis. All participants in the treatment arm will be assumed to have received the full dose of the telephone intervention and all participants in the attention-control arm will be assumed to have received no tailored intervention. Prior to testing for intervention effects, we will verify the comparability of the treatment and control arms with respect to all available demographic and personal data. T-tests and chi-square tests will be used for continuous and categorical variables, respectively. Thus, receipt of sleep apnea assessments within the 6-month period will be a binary outcome, yes or no. We will use logistic regression to estimate the odds associated with receipt of sleep apnea assessment contrasting the two study arms.

### Hypothesis 2

TTI will lead to higher adherence rates to recommended follow-up care (that is, CPAP use (> 4 hours a night for 70% of the nights)) post-diagnosis of sleep apnea.

#### Analysis for hypothesis 2

The analysis plan is similar to that for hypothesis 1. The focus will be on adherence to recommended CPAP treatment. We will use logistic regression to estimate the likelihood of adhering to prescribed CPAP treatment after a diagnosis of sleep apnea was made.

### Hypothesis 3

Effects of the intervention in maintaining adherence will be sustained 6 months after active interventions and interventions will improve clinical outcome measures (WC, BP, HDL-C, and FPG/HbA1c).

#### Analysis for hypothesis 3

We will test the hypothesis that participants in the intervention arm will sustain gains from the initial interactions with the HE, leading to long-term adherence to recommended treatment and follow-up care. It is routinely recommended that participants with sleep apnea return for a follow-up visit after initiating treatments, during which adherence to treatment plan and improvement in sleep parameters is assessed. In our protocol, clinical outcomes (WC, BP, HDL-C, and FPG/HbA1c) will be ascertained post treatment. The analysis plan to test adherence at 6 months post-randomization is similar as for hypotheses 1 and 2; participants returning for a follow-up visit will be grouped as long-term adherents versus non-adherents. Chi-square tests and logistic regression analyses will be used. Repeated-measures MANCOVA will be employed to examine differences between baseline and post-intervention measures (WC, BP, HDL-C, and FPB/HbA1c). *Post hoc* comparisons between groups will be performed with Bonferroni corrections, where univariate results are significant. As required by assumptions governing the use of ANOVA, and since we expect the dependent variables to be modestly correlated, we will first examine their collinearity. Next, normality of the distribution of each measure will be examined and transformations will be performed for non-gaussian distributions. In exploratory analyses, we will determine whether mixed effect modeling would support ANOVA results.

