The primary aim of this on-going randomized trial is to assess the efficacy of a culturally and linguistically tailored telephone-delivered intervention to increase adherence to physician-recommended assessment and treatment of sleep apnea. The secondary aims are to: 1) evaluate the maintenance of intervention effects on adherence at 6 months post-randomization; and 2) assess treatment effects on indices of the metabolic syndrome (waist circumference, blood pressure (BP), lipid levels and fasting plasma glucose (FPG) or hemoglobin (HbA1c) for those who have a DM diagnosis). There are four main hypotheses for this study: 1) participants will show greater adherence to physician-recommended polysomnographic sleep apnea evaluation during follow-up assessment; 2) participants will show greater adherence to CPAP treatment during follow-up assessment; 3) effects of the intervention on adherence rates will be maintained 6 months after discontinuing active interventions, and treatments will improve indexes of the metabolic syndrome; and 4) participants’ knowledge about sleep, self-efficacy, readiness, and trust/rapport with the health educator (HE) will mediate intervention effects on study outcomes. The study is registered in clinicaltrials.gov.

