### Power and sample size calculations

Data obtained from a random sample of black participants recruited from the MetSO Cohort Study has provided a current estimate of the rate of comprehensive assessment of sleep apnea to be expected in the proposed study. Analysis of the data suggested that 47% of participants referred for sleep assessment would adhere to physician recommendations after exposure to TTI, whereas 35% of those in a control group agreed to undergo a sleep assessment. Thus, this represents the likely rate of adherence expected in our AC group. We propose to achieve an adherence rate of 47% among participants exposed to the TTI.

With an expected 12% increase in the adherence rate associated with the TTI, a standard error of 0.10%, and a sample size of 340, the study will be adequately powered (90%) to detect significant increase in the outcome measures using chi-square tests. The primary study outcome in this project is documented receipt of a sleep apnea assessment. A two-tailed test, with alpha = 0.05, comparing adherence rates of 35% with 47% requires 170 participants per group [42]. The precision estimated in that analysis is the approximate expected precision of study data. Specifically, a difference of 12% would be observed at chi-square = 21.03 with a 95.0% confidence interval of 3% to 20%. With the proposed sample size, the study will have 85% power to achieve a one-standard deviation increase in the odds ratio of adherence attributable to proposed mediators: sleep apnea knowledge, self-efficacy, readiness, and trust/rapport with the HE (expressed as continuous variables).

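### Hypothesis 4 claims that the scores mediate the TTI effect, but the stated mediator analysis and its power address only whether the scores are associated with adherence

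*Protocol article*

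**What the plan says.** The Background section of the protocol article lists four main hypotheses. The fourth is that "participants’ knowledge about sleep, self-efficacy, readiness, and trust/rapport with the health educator (HE) will mediate intervention effects on study outcomes".

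The Statistical analysis section gives the method in its opening overview: "Relationships between mediators of adherence to recommended sleep apnea assessment and CPAP treatment will be examined using binary multivariate logistic regression analysis". It names the outcomes of that analysis: "The two main dependent measures will be: adherence to physician-recommended sleep assessment (yes versus no) and adherence to CPAP treatment (yes versus no"). It names the predictors: "Candidate mediators will include sleep apnea knowledge, self-efficacy, readiness, and trust/rapport with the HE". On covariates it says: "Effects of sociodemographic and clinical factors will be adjusted in those analyses".

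Arm appears in a separate model, for hypothesis 1: "We will use logistic regression to estimate the odds associated with receipt of sleep apnea assessment contrasting the two study arms". No mediator is named there. Hypotheses 1 to 3 each have an analysis subsection; hypothesis 4 has none. The repeated-measures MANCOVA for change from baseline is illustrated only with waist circumference, blood pressure, HDL-C and glucose/HbA1c.

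The Power and sample size section gives 85% power for an "increase in the odds ratio of adherence attributable to proposed mediators: sleep apnea knowledge, self-efficacy, readiness, and trust/rapport with the HE", with the mediators as continuous variables. No numerical odds ratio is given.

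**The concern.** Mediation needs two links: TTI must change the score, and the score must affect adherence at a given arm. The null of hypothesis 4 is that at least one link is absent. The stated regression has a different null, that the score is unrelated to adherence. People who know more or feel more confident may well attend more often in either arm. A score can therefore predict adherence strongly while TTI does nothing to it.

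The risk is that hypothesis 4 is declared supported by a test that does not address it, and that TTI is then explained and disseminated on the strength of pathways it may not use. The problem lies in the choice of null. It would remain even if every score were measured at the ideal time in both arms.

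**Working it through.** **1. Which model covers which link**

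| Link | Model named in the article |
|---|---|
| Arm → adherence (total effect) | Logistic regression, hypotheses 1 and 2 |
| Mediator → adherence | Logistic regression on mediators, adjusted for sociodemographic and clinical factors; arm not named |
| Arm → mediator | None named |
| Indirect effect | None named |

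**2. What the 85% power refers to**

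The figure cannot be reproduced directly because no odds ratio is stated. Reading it as power per SD of one continuous mediator, it can be inverted:

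ln(OR) = (z₀.₉₇₅ + z₀.₈₅) / √(N·p·(1 − p)), with N = 340, two-sided alpha 0.05, and p between the planned adherence rates of 35% and 47%.

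- p = 0.35: N·p·(1 − p) = 77.35, square root 8.795; ln(OR) = (1.960 + 1.036)/8.795 = 0.341; OR = 1.41.
- p = 0.47: N·p·(1 − p) = 84.69, square root 9.203; ln(OR) = 2.996/9.203 = 0.326; OR = 1.38.

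So the stated power corresponds to an odds ratio of about 1.4 per SD between score and adherence. The effect of TTI on the score does not enter the calculation.

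**3. How often the stated test is significant when nothing is mediated**

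Inputs from the article: 170 per arm, control adherence 35%, two-sided 5%. Assumptions: one mediator, no other covariates, and the odds ratios per SD below.

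Model: score m = a·arm + N(0,1); logit P(adherent) = c + d·arm + ln(OR)·m, with c set to give 35% in control.

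Here a = 0, so TTI does not move the score. The direct arm effect d was set to 0 or about 0.5. The latter matches the planned contrast: ln(0.47/0.53) − ln(0.35/0.65) = −0.120 + 0.619 = 0.499.

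Ranges below are over independent simulations of 2,000 to 4,000 runs per setting.

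| OR per SD (assumed) | Mediator coefficient significant | Also requiring an arm effect on the score |
|---|---|---|
| 1.2 | 34% to 36% | about 2% |
| 1.4 | 82% to 85% | about 4% to 5% |
| 1.5 | 93% to 94% | about 4% to 5% |

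Putting arm in the adherence model does not change this. In one set of runs with d = 0.5 and OR 1.4, the rate was 84.7% without arm and 84.4% with it.

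**4. Power of the two-link requirement when mediation is real**

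- TTI shifts the score by 0.5 SD, OR 1.5: about 94%.
- TTI shifts the score by 0.3 SD, OR 1.4: about 66%, against about 84% for the mediator coefficient alone.

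**5. Where the missing link can be tested**

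Table 2 schedules the apnea knowledge test and the self-efficacy scale at baseline and first follow-up. The Change assessment scale, the readiness instrument, is scheduled at baseline only. Under the attention-control arm, calls come from a research assistant rather than the health educator (HE), so trust/rapport with the HE has no evident control counterpart.

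**The case against.** A journal article condenses the plan, and the path models of a mediation analysis are commonly left to the statistical analysis plan. The article does not exclude arm from the mediator model. The MANCOVA measures are introduced as examples, and knowledge and self-efficacy are collected twice, so a between-arm comparison of change is possible. A reader might infer that the trial will never test whether TTI moves these scores. The document does not support that: it is silent, and silence in an article is not a decision.

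Nor does the article state a rule for declaring mediation. It says that relationships of candidate mediators will be examined. A reader might infer that the trial will falsely report mediation in up to 94% of cases. That is not supported either. The percentages are the ordinary power of an association test when the association is real. They become false-claim rates only if a significant coefficient is read as support for hypothesis 4. Where TTI also has no effect on adherence, a mediation claim would have to ignore a null result for hypothesis 1.

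The article's remark that higher scores go with likelier adherence concerns the Apnea Beliefs Scale, which is not one of the four named mediators, so it is no evidence here.

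These points limit the size and certainty of the finding but do not remove it. The article does not leave the method open: it fixes a regression, its outcomes, its covariates and its power, and all of these concern the mediator-adherence association. That is a method mismatched to its hypothesis, not just omitted detail.

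**Conclusion.** The stated mediator analysis and its 85% power do not address hypothesis 4. They can identify predictors of adherence. If a significant coefficient is taken as support for mediation, the error rate when TTI leaves the score unchanged is about 34% to 36% at OR 1.2 per SD and 82% to 85% at OR 1.4, against about 2% to 5% when an arm effect on the score is also required.

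These figures rest on assumed odds ratios, a single mediator without other covariates, and all 340 participants. They do not carry over to CPAP adherence, which is analysed only after a diagnosis and so in a smaller group. The OR of 1.4 rests on reading the 85% as power per SD of mediator.

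The primary outcome, the arm contrast and the sample size are not affected. The point should be corrected because hypothesis 4 is presented as a main hypothesis and the correction is cheap.

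**What to change.** In the Statistical analysis section, add a subsection for hypothesis 4 covering mediators measured at follow-up in both arms (knowledge and self-efficacy, as scheduled):

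1. Regress the follow-up score on arm, adjusting for its baseline value.
2. Fit logistic regression of adherence on arm, follow-up score, baseline score and the planned covariates.
3. Claim mediation only if both paths are significant, or if the confidence interval of the indirect effect excludes zero. A bootstrap interval on the risk-difference scale is one acceptable choice.
4. State the assumption of no unmeasured confounding between mediator and adherence.

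Label the existing regression as an analysis of predictors of adherence, and describe the 85% in the Power and sample size section as power for that association. As scheduled, make no mediation claim for readiness or for trust/rapport with the HE.

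The cost is wording and modest programming, with no new data for knowledge and self-efficacy. The downside is that fewer mediation claims will be supported and power is lower: about 66% at a 0.3 SD shift and OR 1.4, and about 94% at 0.5 SD and OR 1.5.
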